### Measurements

All analytical measurements were performed in a central laboratory at the Texas Diabetes Institute (San Antonio, TX). Plasma glucose concentration was measured by the glucose oxidase reaction (Glucose Oxidase Analyzer, Beckman Instruments, Fullerton, CA). Plasma insulin was measured by radioimmunoassay (Diagnostic Products, Los Angeles, CA). The interassay and intra-assay CVs for the insulin assay are 7.1% and 5.1%, respectively. Plasma C-peptide was measured by radioimmunoassay (Diagnostic Systems, Webster, TX). The interassay and intra-assay CVs for the C-peptide assay are 2.4% and 4.3%, respectively. HbA_1c _was measured by an ion-exchange HPLC instrument (Bayer DCA 2000, Leverkusen, Germany). Total plasma cholesterol and triglycerides were measured using the CHOD-DAOS method (WAKO, Richmond, VA) and an enzymatic assay (Stanbio Lab, Boerne, TX). HDL cholesterol was measured after precipitation of apolipoprotein B-containing lipoproteins with dextran sulfate-Mg^++^, using the CHOD-DAOS method (WAKO, Richmond, VA). LDL cholesterol was calculated by the Friedewald equation.

### Calculations

Incremental area under the curve (AUC) for plasma glucose and insulin concentrations during the OGTT was calculated according to the trapezoidal rule. The insulinogenic index was calculated as ΔI(AUC)/ΔG(AUC) from 0–30 and 0–120 minutes [21,22]. The insulin secretory rate during the OGTT was calculated by deconvolution of the plasma C-peptide curve [34] and expressed as ISR/ΔG [21,22,35].

During the FSIVGTT, first phase insulin secretion was calculated as the increment in plasma insulin concentration (AUC) above baseline from 0–10 minutes and as the peak increment in plasma insulin concentration (minus baseline) during the 0–10 minute time period. Indices of insulin sensitivity (S_I_) and glucose effectiveness (S_G_) were determined by minimal model analysis of insulin and glucose concentrations during the FSIVGTT as previously described [32].

The insulin secretion/insulin resistance or disposition index during the OGTT was calculated as ΔI/ΔG × Matsuda index and as ΔI/ΔG × S_I _[32,36]. The hepatic insulin resistance index was calculated as the FPI × FPG (equivalent to inverse of HOMA) [37]. The basal adipocyte insulin resistance index was calculated as the fasting plasma insulin (FPI) × fasting plasma FFA concentrations [38].

### Statistical Analysis and Sample Size

General Statistical Plan: Analysis of primary and secondary endpoints will utilize the intent-to-treat approach [39]. All participants will be included in their randomly assigned pioglitazone or placebo treatment groups. All statistical tests will be two-sided and require alpha = 0.05 to be considered significant.

#### Primary and Secondary Endpoints

The ***primary endpoint ***is the development of diabetes mellitus according to ADA criteria [29]. Accordingly, the principal analysis will be a life-table analysis of the time from randomization to the confirmed development of diabetes. Separate life-table estimated cumulative incidence curves will be calculated for the pioglitazone-treated and placebo-treated groups, which will be compared using a logrank test [38,40]. Subjects who are lost to follow up or who prematurely decide to drop out of the study will be categorized according to data obtained up to their last follow-up visit.

Secondary outcomes (i.e., cardiovascular events and mortality) will be compared using the same life-table analysis described above for the primary endpoints.

Repeated measures data (i.e., FPG, 2-hour plasma glucose during OGTT, HbA_1c_, measures of insulin secretion and insulin sensitivity, plasma lipids and other cardiovascular risk factors, blood pressure, carotid initmal media thickness, body weight and BMI, measures of fat mass and fat topography) will be compared between the pioglitazone-treated and placebo-treated groups using longitudinal data methods: (i) point prevalence of a discrete characteristic (i.e., normal or impaired glucose tolerance) at repeated visits over time [40] and (ii) multivariate rank analysis of quantitative (i.e., FPG, 2-hour plasma glucose, HbA_1c_, plasma lipids, plasma cardiovascular risk factors, etc) variables over repeated visits [40]. Differences in slopes over time (i.e., rate of change in FPG, 2-hour plasma glucose, HbA_1c_, plasma lipids, etc) between pioglitazone-treated and placebo-treated groups will be compared by the parametric linear random effects model [41].

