## Background

Type 2 diabetes mellitus (T2DM) affects 21 million Americans [1] and approximately 194 million individuals world wide [2] and its prevalence is rapidly increasing [3]. Microvascular [4] and macrovascular [5] complications are common in T2DM and both are strongly related to the severity and duration of hyperglycemia [6-8]. The estimated cost for the treatment of T2DM and related complications in year 2007 was 174 billion dollars [9].

The natural history of T2DM has been well defined [10-14], starting with a genetic predisposition and progression from normal glucose tolerance with insulin resistance to impaired glucose tolerance with superimposition of beta cell failure on insulin resistance, and eventually to overt T2DM characterized by severe beta cell failure and insulin resistance.

Because of the central role that hyperglycemia plays in the development of both micro- and macrovascular complications [4-8], it follows that interventions designed to prevent or delay the onset of hyperglycemia would be effective in preventing these long term complications. Recent studies have demonstrated that life style modification [15,16] and therapy with metformin [16] and thiazolidinediones [14,17,18] can prevent or delay the onset of T2DM in high risk subjects. Individuals with impaired glucose tolerance (IGT) represent a high risk group, with a conversion rate that varies from 3–13% per year, depending upon the ethnic group [19].

Individuals with IGT are characterized by defects in both insulin secretion and insulin sensitivity [20-22]. Therefore, interventions designed to enhance beta cell function and ameliorate insulin resistance would be expected to be effective in preventing the progression of IGT to T2DM. Pioglitazone and other thiazolidinediones have been shown both to enhance muscle/hepatic/adipocyte insulin sensitivity [23-26] and to improve beta cell function [16,18,27,28]. Because thiazolidinediones reverse the characteristic defects present in IGT and T2DM, they represent a logical choice to prevent/delay the onset of diabetes in high risk individuals.

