Thiazide diuretics at a dose greater than 25 mg/day
Non-cardioselective beta-blockers (individuals receiving treatment with a statin or fenofibrate will not be excluded as long as the dose has been stable for 3 months prior to randomization)
Glucocorticoids, systemic
Prescription weight-loss or weight-gain medications
• Thyroid disease, suboptimally treated as indicated by abnormal serum thyroid-stimulating hormone
• Other endocrine disorders (e.g. Cushing's syndrome, acromegaly)
• Fasting plasma triglyceride > 400 mg/dl, despite treatment
• Individuals with a history of bladder cancer
• Individuals with hematuria at screening. However, subjects with hematuria may be randomized if the cause of the hematuria is found, treated, and thought unlikely to recur.

During the course of recruitment, the investigators agreed to modify the glycemic inclusion criteria to allow enrollment of persons with fasting glucose of 90–125 mg/dl as long as the 2-hour plasma glucose concentration was 170–199 mg/dl, in recognition of the high risk of diabetes in such persons.

Eight centers took part in the study and the protocol was approved by the individual IRB of the 8 participating centers. After ascertaining eligibility and collection of baseline measures as described below, subjects were randomized by center and gender using block randomization to ensure equal distribution. Prior to randomization all subjects met with a dietician and received 30 minutes of instruction consistent with the goals of the Diabetes Prevention Program [16]. These goals emphasized reduced total caloric intake, decreased fat intake, and walking 30 minutes per day for 4–5 days per week. Goals were reinforced on all follow up visits.

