Potentially eligible IGT subjects (n = 1850) were identified according to recruitment procedures most suited to each of the 8 participating centers and their written, voluntary informed consent was obtained. Subjects then received a 75 gram oral glucose tolerance test (OGTT) with samples drawn at -30, -15, 0, and every 15 minutes thereafter for 2 hours for determination of plasma glucose, insulin, C-peptide, and free fatty acid concentrations. The OGTT was performed at 0800 h following an overnight fast (after 2000 h). Samples for determination of plasma glucose concentration were sent to the Central Laboratory (Texas Diabetes Institute, San Antonio, TX) and sites were notified about subject eligibility (FPG ≥ 95 mg/dl and 2-h PG = 140–199 mg/dl) within 48 hours. Subjects meeting these criteria returned for a medical history, physical examination, screening blood tests (chemistries and complete blood cell count), urinalysis, and electrocardiogram. During this visit or on a subsequent visit prior to randomization, a fasting blood sample was obtained for the measurement of HbA_1c_, and lipid profile, and plasma and serum were collected for later measurement of novel risk factors. The first voided morning urine specimen was collected for determination of microalbumin to creatinine ratio and a 24-hour urine was collected for determination of 8-epi-prostaglandin F_2_α (also termed 15-F_2t_-IsoP), a measure of oxidative stress [30]. Systolic and diastolic blood pressures were measured with an automated Dinamap Pro 100 instrument (GE Medical Systems, Milwaukee, WI) following 5 minutes in the reclining position and after 5 minutes in the upright position. Ankle-arm blood pressure was measured as described by Papamichael et al [31].

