#### Sample Size

The conversion rate of IGT to diabetes varies considerably based upon ethnicity and a number of other risk factors. The DPP [42] cited 21 studies with conversion rates (percent per year) ranging from 2.3% to 11%. In addition, they evaluated data sets from six population based cohorts [43]. The conversion rate from IGT to diabetes in these six studies was 5.8 per 100 person-years for follow-up and rose to 8.2 per 100 person-years for individuals with a fasting plasma glucose concentration > 100 mg/dl. In certain ethnic groups, (i.e., Latinos with a history of GDM), much higher conversion rates of IGT to diabetes (14.3% per year) have been reported [18,44]. The DPP [15] demonstrated a conversion rate of IGT to diabetes of approximately 11% per year. In the group of IGT subjects treated with diet/exercise and metformin, the conversion rates were decreased by 58% and 31%, respectively. In the TRIPOD study [18], GDM women treated with placebo converted to diabetes at a rate of 12.1% per year and this rate was decreased to 5.4% in the troglitazone-treated group. Based upon this information (see assumptions below), it can be calculated that approximately 600 subjects with IGT will be required to achieve 90% statistical power that pioglitazone decreases the conversion rate of IGT to type 2 diabetes by 50%. This power calculation assumes that randomized individuals drop out prior to the confirmed diagnosis of diabetes with an exponential hazard rate of 0.10 (or less) per year.

The following assumptions were used to calculate the sample size:

(i) The primary endpoint is the development of diabetes,

(ii) Participants are randomized over a 21 month period and followed for a total of 3.75 years, starting from the time that the first IGT subject is recruited,

(iii) Type I error rate (alpha) is 0.05,

(iv) The desired power is 90%,

(v) The development of diabetes in the placebo-treated group is 11% per year,

(vi) The hazard rate for the development of diabetes in the pioglitazone-treated group is reduced by 50%.

(vii) The drop out rate is 10% per year

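### As stated, the primary logrank test uses neither the randomisation factors (centre, gender) nor entry glucose: a modest loss of efficiency, not a bias

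*Protocol article*

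**What the plan says.** - **Primary analysis** (Primary and Secondary Endpoints): a life-table analysis of time from randomisation to confirmed diabetes. "Separate life-table estimated cumulative incidence curves will be calculated for the pioglitazone-treated and placebo-treated groups, which will be compared using a logrank test". Neither this section nor the rest of Statistical Analysis and Sample Size names a stratum, covariate or adjusted model for this endpoint.
- **Randomisation** (Overall Study Design/Subject Eligibility, text after Table 1): "Eight centers took part in the study", and "subjects were randomized by center and gender using block randomization to ensure equal distribution". That gives 8 × 2 = 16 strata.
- **Entry glucose** (same section): every candidate had an oral glucose tolerance test read by the central laboratory, after which "sites were notified about subject eligibility (FPG ≥ 95 mg/dl and 2-h PG = 140–199 mg/dl) within 48 hours".
- **Glucose as a predictor**: Sample Size gives 5.8 conversions per 100 person-years in six cohorts, and 8.2 in those with fasting glucose above 100 mg/dl. During recruitment the fasting limit was lowered to 90 mg/dl for people with 2-hour glucose of 170–199 mg/dl, because the investigators judged them to be at high risk.

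**The concern.** The design treats centre and gender as important enough to balance, yet the stated analysis does not use them. Entry glucose is a stronger candidate. Entry ranges stop at 125 mg/dl fasting and 199 mg/dl at 2 hours, and the endpoint begins at 126 and 200, so the baseline value and the outcome are the same measurement. Glucose was not a randomisation factor, and the entry rule for it changed partway through recruitment.

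With a time-to-event outcome, leaving out strong baseline predictors costs power. The information is already held on everyone, so the question is how much power is given up.

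**Working it through.** **Inputs from the article.** Two-sided alpha 0.05, power 90%, hazard ratio 0.5, placebo rate 11% per year, dropout hazard 0.10 per year, accrual 1.75 years, total duration 3.75 years. Equal allocation is assumed, since no ratio is given.

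**Step 1: the plan's own sample size.** With (1.960 + 1.282)² = 10.51:

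- Schoenfeld events: 4 × 10.51 / (ln 0.5)² = 42.03 / 0.4805, rounded up to 88.
- Freedman events: 10.51 × (1.5 / 0.5)² = 94.6, rounded up to 95.

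For diabetes hazard λ, dropout hazard η, s = λ + η, accrual R and duration T, the event probability is (λ/s) × {1 − [exp(−s(T−R)) − exp(−sT)] / (sR)}.

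- Placebo (λ = 0.11, s = 0.21): 0.5238 × [1 − (0.6570 − 0.4550)/0.3675] = 0.236.
- Pioglitazone (λ = 0.055, s = 0.155): 0.3548 × [1 − (0.7334 − 0.5592)/0.27125] = 0.127.
- Mean 0.1813. Required N is 88/0.1813, or 486 (Schoenfeld), and 95/0.1813, or 524 (Freedman).

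The stated figure of about 600 comes out if N is found without dropout and then inflated. Freedman gives 457 without dropout, and 457/exp(−0.10 × 2.875) = 457/0.750, or 610. With 600 subjects under exponential dropout, expected events are 600 × 0.1813 = 109. Power is then 93.5% (Freedman) to 95.1% (Schoenfeld).

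**Step 2: what using the baseline data would add.** Trials of 600 subjects were simulated in 16 centre-by-gender strata with blocks of 4, 1,500–2,000 runs per scenario (Monte Carlo standard error about 0.5–0.8 points). The prognostic strengths are assumptions, because the article gives none for this population. Power at hazard ratio 0.5:

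| Assumed prognosis | Unstratified logrank | Logrank stratified by centre and gender | Cox with glucose, centre, gender |
|---|---|---|---|
| None | 94% | 94% | 94% |
| Centre SD 0.3, gender log-HR 0.2, glucose HR 1.3 per SD | 93.0% | 92.7% | 93.2% |
| Same, glucose HR 1.5 | 92–93% | 93% | 94% |
| Centre SD 0.5, gender log-HR 0.4, glucose HR 1.5 | 91–92% | 91–92% | 93% |
| Same, glucose HR 2.0 | 87–88% | 88% | 92–93% |

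Stratification alone moves power by −1 to +1 point. Nearly all the gain comes from glucose. At hazard ratio 0.6 the adjusted Cox model gains about 2–8 points where prognostic effects are assumed and nothing where they are absent.

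**Step 3: validity.** With no treatment effect, the unstratified test rejected in 4.2–5.7% of trials. At 5% and 1,500 runs the standard error is √(0.05 × 0.95/1,500) = 0.56 points, so neither inflation nor conservatism is shown. In one set of 1,500 runs the adjusted Cox test rejected in 5.3–6.4%. Its upper values lie slightly above nominal, so part of the small gain in the moderate rows may not be real.

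**Step 4: chance imbalance in glucose.** With 301 per arm, an imbalance of 1.96 standard errors is 1.96 × √(2/301) = 0.16 SD. At an assumed glucose hazard ratio of 1.5 per SD this is a factor of exp(0.16 × ln 1.5) = 1.067, which would move an estimate of 0.50 to about 0.47 or 0.53.

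**The case against.** **The article is condensed.** It says a logrank test, not an unstratified one, and a fuller plan could add strata. This stands as a limit on wording: the point applies to the analysis as stated here. It does not remove the point, because the article names its principal comparison and a better one is available from data already held.

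**The benefit is small.** This also stands. At the plan's own assumptions power is already above 90%, and stratifying by centre and gender gains nothing worth having. A separate simulation at 8.2% per year gave larger gains, up to 78 to 85% at hazard ratio 0.5 and 54 to 62% at 0.6. Those used a lower rate than planned and an assumed log-hazard SD of 1.0 for glucose, a hazard ratio of exp(1.0) = 2.7 per SD. The article does not support a value that strong, and its narrow entry range for fasting glucose limits the spread.

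**Stronger readings a reader might infer are not supported:**

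- *That the stated test is biased, because its hazard ratio sits closer to 1.* In simulation 0.50 drifted to 0.51–0.53. That is the difference between a covariate-conditional and a group-level hazard ratio (non-collapsibility). The planned 50% reduction is stated at group level.
- *That ignoring the blocking makes the test conservative.* The rejection rates above do not show it.
- *That chance imbalance in glucose invalidates the comparison.* Randomisation already allows for it in the type I error; adjustment only improves precision.
- *That centres must differ widely in risk.* The Background describes IGT populations "with a conversion rate that varies from 3–13% per year, depending upon the ethnic group", but no centre's ethnic mix is given. Even with centre rates spanning that ratio, power was 87.8% unstratified and 87.6% stratified at 8.2% per year.

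**Conclusion.** The point holds as a minor one. As stated in the article, the primary test leaves out the two randomisation factors and the two baseline measurements most closely tied to the endpoint. The test remains valid at the declared two-sided 5% level. The cost is a mismatch with the randomisation and some lost power: about 0–2 points at hazard ratio 0.5 under moderate prognostic effects, about 5 under very strong ones, and about 2–8 at hazard ratio 0.6 where such effects are assumed. These sizes rest on assumed prognostic strengths. The article supports the direction for glucose (8.2/5.8 = 1.41, and the first figure includes people above 100 mg/dl) but not the strength per SD. The case for the change is that it costs no data and protects power if the true effect is smaller than planned.

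**What to change.** Before the treatment code is broken:

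- Make the primary comparison the treatment test from a Cox model stratified by (or adjusted for) centre and gender, with baseline fasting and 2-hour glucose as continuous covariates. Glucose must be in the primary test itself. A logrank test stratified by centre and gender alone would not capture the gain.
- State the test statistic in advance, given the slightly high null rejection seen for the adjusted model.
- Set any pooling of small centres by blinded enrolment counts, not by events. About 109 expected events over 16 strata is roughly 7 per stratum, so a rule is needed.
- Report the hazard ratio as conditional on the covariates.
- Keep the unstratified logrank test and the life-table curves as supporting analyses.

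The cost is a short, dated change to the analysis text and no new data. Because it alters a named primary test after enrolment has closed, it counts as pre-specified only if documented while blinded. Otherwise the adjusted model should be reported as a sensitivity analysis beside the stated logrank test.

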### Secondary Objectives

Secondary objectives include whether pioglitazone can: (i) improve glycemic control; (ii) enhance insulin sensitivity; (iii) improve beta cell function; (iv) improve risk factors for cardiovascular disease; (v) cause regression/slow progression of carotid intima-media thickness, (vi) decrease microalbuminura; (vii) revert newly diagnosed type 2 diabetic subjects to a state of normal glucose tolerance.

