At 8 AM on a separate day subjects from seven centers had a measurement of carotid intimal media thickness (IMT) using B-mode ultrasound (Logiq, GE Medical Systems, Milwaukee, WI) [33]. A standardized protocol was followed by all centers to assure quality control. Prior to initiation of the study, all ultrasound technologists received training at the coordinating center, directed by [name] at the University of Southern California, to ensure uniformity of measurement amongst centers. Acquisition of an image of the far wall of the common carotid was obtained and carotid IMT scans were sent to the coordinating center, where they were read blindly by two readers, as previously described [33]. In a subset of subjects at 7 of the 8 centers a second measurement was performed within 2 weeks of the initial scan to determine reproducibility and technologist performance. The coefficient of variation of these two measurements was 0.72% (range = 0.14–0.90). Carotid IMT measurements also were performed at mid study and at study end (or at time of diagnosis of diabetes) to examine the rate of change in carotid IMT.

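### The level comparison of quantitative secondary variables names no baseline value or randomisation factor, and the companion slope test is a weak substitute for variables measured at every visit

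*Protocol article*

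**What the plan says.** The Primary and Secondary Endpoints section of the protocol article lists the repeated-measures variables: glucose measures, HbA1c, insulin secretion and sensitivity, lipids and other risk factors, blood pressure, carotid IMT, weight and BMI, and fat measures. It names two between-arm methods for the quantitative ones.

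- Item (ii) is a "multivariate rank analysis of quantitative (i.e., FPG, 2-hour plasma glucose, HbA_1c_, plasma lipids, plasma cardiovascular risk factors, etc) variables over repeated visits".
- The next sentence adds a second comparison: "Differences in slopes over time (i.e., rate of change in FPG, 2-hour plasma glucose, HbA_1c_, plasma lipids, etc") "will be compared by the parametric linear random effects model".

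No baseline covariate, centre or gender term is named for either. Both method lists end in an open-ended etc., so IMT, weight and blood pressure come under them only by implication.

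The Overall Study Design/Subject Eligibility section supplies what could be used for adjustment. In the text after Table 1, "subjects were randomized by center and gender using block randomization to ensure equal distribution". Before randomisation "a fasting blood sample was obtained for the measurement of HbA_1c_, and lipid profile", and weight, waist, blood pressure and IMT were also measured at baseline.

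For IMT, the Secondary Objectives section asks whether pioglitazone can "cause regression/slow progression of carotid intima-media thickness", and the design section says the scans were repeated "to examine the rate of change in carotid IMT".

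**The concern.** Metabolic variables usually differ more between people than a treatment moves them within a person. A comparison of follow-up levels that leaves out each subject's own starting value carries all of that between-subject spread as noise. The section contrasts the ranked variables with their rate of change in the next sentence, so levels is the natural reading of item (ii).

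The slope model does use within-subject information, but it answers a different question. If the effect appears early and then stays constant, the arms run parallel for most of follow-up and a fitted line captures little of it. An early effect is plausible here, because the Recruitment and Following Visits section has the dose reach its maximum after one month if no adverse events were present. In that setting one planned test is inefficient and the other looks for the wrong shape. A real effect on glycaemia, weight or cardiovascular risk factors could be missed although the data to detect it were collected.

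**Working it through.** **The plan's own figure.** There is none to reproduce. The only sample-size calculation concerns conversion to diabetes. The article gives no SD, correlation or power for a quantitative secondary variable, so everything below rests on stated assumptions.

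**Step 1: one follow-up value.** With baseline-to-follow-up correlation r (assumed), adjustment leaves 1 − r² of the variance and removes r².

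| r | removed | sample-size equivalent, 1/(1 − r²) |
|---|---|---|
| 0.3 | 9% | 1.10 |
| 0.5 | 25% | 1.33 |
| 0.7 | 49% | 1.96 |
| 0.9 | 81% | 5.26 |

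**Step 2: several visits, and whether the slope test rescues the loss.**

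Inputs:
- From the article: two-sided alpha 0.05, about 600 subjects and so 300 per arm, and the visit schedule.
- Assumed: a constant shift of 0.15 SD from the first post-baseline visit, equal correlation r between all visits, follow-up to month 36, no dropout or conversion.

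Formulas in SD units, with k follow-up visits at times t (baseline t = 0), mean time t̄ and Sxx = Σ(t − t̄)² taken over all visits including baseline:
- Variance of a subject's follow-up mean: v = (1 + (k − 1)r)/k.
- Unadjusted levels: z = 0.15/√(2v/300).
- Baseline-adjusted levels: z = 0.15/√(2(v − r²)/300).
- Slopes: a step after baseline gives an expected slope difference of 0.15·t̄/Sxx, and the slope variance is (1 − r)/Sxx. Hence z = 0.15·(t̄/√Sxx)/√(2(1 − r)/300).
- Power = Φ(z − 1.96).

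*Variables measured at every visit* (fasting glucose, weight, blood pressure, waist): months 1, 2, 4, 6, 8, 10, 12, then every 3 months to 36. So k = 15, t̄ = 247/16 = 15.44, Sxx = 5945 − 247²/16 = 2131.9, t̄/√Sxx = 0.334.

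At r = 0.5, v = 8/15 = 0.533:
- unadjusted: z = 0.15/0.0596 = 2.52, power 71%
- adjusted: variance 0.533 − 0.25 = 0.283, z = 0.15/0.0435 = 3.45, power 93%
- slopes: z = 0.15 × 0.334/0.0577 = 0.87, power 14%

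*Variables measured yearly* (2-hour glucose, HbA1c): years 1, 2 and 3. So k = 3, t̄ = 1.5, Sxx = 5, t̄/√Sxx = 0.671.

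| Schedule | r | unadjusted levels | adjusted levels | slopes |
|---|---|---|---|---|
| Every visit | 0.5 | 71% | 93% | 14% |
| Every visit | 0.7 | 58% | 97% | 20% |
| Every visit | 0.9 | 49% | 100% | 49% |
| Yearly | 0.5 | 61% | 81% | 41% |
| Yearly | 0.7 | 54% | 91% | 61% |
| Yearly | 0.9 | 48% | 99.9% | 97% |

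These formulas treat means. Simulations with rank tests and a two-stage slope test in place of the random-effects model (1,000 runs, same assumptions) agree within a few points: 71/93/14% at r = 0.5 and 49/100/48% at r = 0.9 on the frequent schedule, and 60/77/41% and 46/99.7/97% with yearly visits.

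**Reading the results.** The slope test recovers the loss only where visits are sparse and r is high. With frequent visits it falls far short of the adjusted comparison at all three correlations.

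**Centre and gender.** The document offers nothing from which to derive a gain for these, and none is claimed. They belong in the analysis because allocation was balanced on them.

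**The case against.** The strongest reply is that the article does not say baseline is ignored. It says only that the variables are analysed over repeated visits; it does not exclude the baseline visit, change scores or stratified ranks, and the full protocol and statistical analysis plan are not shown. An article commonly leaves covariates to those documents. This stands in part: silence is not proof, and if those documents already adjust, the remedy is one clarifying sentence. What remains is that the article does name its methods, and a baseline-adjusted comparison is better than the level comparison as named.

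It is also fair that unadjusted randomised comparisons are valid. Chance baseline imbalance is covered by the type I error rate and is not bias. Rank methods are a reasonable choice for skewed variables.

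Three stronger readings are tempting and should not be drawn:

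- A reader might infer that the rank analysis is the only planned comparison and that the plan as a whole discards each subject's own starting point. The slope model in the next sentence uses each subject's trajectory.
- A reader might state the loss as a quarter to nine tenths of the precision. That range only restates assumed correlations of 0.5 to 0.95; at 0.3 the figure is 9%.
- A reader might take IMT as the worst case because "The coefficient of variation of these two measurements was 0.72% (range = 0.14–0.90"). That is scan reproducibility within two weeks, not a correlation over years. The stated aim for IMT is rate of change, which the slope model naturally covers. IMT is scanned only at baseline, at 15–18 months and at the final visit, so if r is high that model would recover most of the loss, as the yearly row at 0.9 suggests.

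**Conclusion.** The point holds as a matter of efficiency for quantitative secondary variables. As written, the level comparison names neither baseline nor the randomisation factors, and for an early, sustained effect on variables measured at every visit the slope test does not compensate. Under the assumptions above, the better of the two planned tests falls short of the adjusted one by 22 points of power at r = 0.5 (93 − 71) and by 51 points at r = 0.9 (100 − 49) on the frequent schedule. With yearly visits the shortfall is 20 points at r = 0.5 (81 − 61) and about 3 at r = 0.9 (99.9 − 97).

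These sizes depend on an assumed correlation, an assumed 0.15 SD shift of constant size, equal correlation between visits and no dropout or conversion. An effect that grows steadily over time would favour the slope test. Type I error is not at issue and the primary endpoint is not affected.

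**What to change.** In the Primary and Secondary Endpoints section:

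1. Replace item (ii) with a baseline-adjusted comparison: a repeated-measures model, or ANCOVA where there is one follow-up value, with the baseline value, centre and gender as covariates. For skewed variables use rank-ANCOVA stratified by centre and gender.
2. Keep the random-effects slope comparison alongside it.
3. Name IMT explicitly, and state that the rate-of-change comparison is the test for secondary objective (v).

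If the full protocol or analysis plan already adjusts in this way, one sentence saying so is enough. The cost is analysis wording and programming; no new data, visits or participants are needed.
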